### Power analysis

A sample size of 25 per treatment condition will provide us with > 99% power to detect an effect size comparable to the large between-condition effect size (*d* = 1.44) observed for attendance from our preliminary 3-week trial in cocaine users [53] with a two-tailed alpha = 0.05. In addition, this sample size will provide 80% power to detect an effect size of 0.81 or greater.

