**Methods/design:**

We are conducting a randomized, double-blind, placebo-controlled trial of oxytocin-enhanced motivational interviewing group therapy (MIGT). Oxytocin or placebo 40 IU is administered intranasally in conjunction with six, weekly MIGT sessions. We will recruit 50 MSM, initiating treatment for MUD from specialized community health programs in San Francisco, CA, USA. Individuals will be randomized (1:1) to receive six, weekly sessions of MIGT with or without oxytocin. Our primary outcome is session attendance. Other outcomes of interest include: measures of group cohesion, anxiety, psychophysiology, and stimulant craving and use.

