The MIGT cohorts in this study will consist of two co-facilitators, one will be a licensed psychiatrist and the other will be a mental health trainee (PhD, PsyD, or psychiatry resident) along with four to six group members. All MIGT sessions will be conducted at the Alliance Health Project in San Francisco, CA, USA. A semi-structured, closed-admission, time-limited (six sessions) OE-MIGT manual for methamphetamine users was developed for this study using guidance from Wagner and Ingersoll (2013) [55]. Included are four brief psychoeducational components for optional use during the first four sessions: stages of change, ambivalence and a decisional balance chart for methamphetamine use, attachment theory and social support, and managing stress. These topics aid in the Engagement and Exploring Perspectives phases of the group, are designed to maximize the effects of intranasally administered oxytocin on MIGT for MUD, and correspond to the specific objectives of this research study. The final two sessions are left unstructured in order to allow more time for Broadening Perspectives and Moving Into Action. Adherence raters will assess session transcripts using motivational interviewing treatment integrity (MITI) 4.2; a coding system designed to measure group facilitators’ adherence to MI [56]. Consistent with previous work by the research team, a fidelity checklist reflecting the content of the session will be developed in order to determine whether the intervention was delivered as intended. Prior to participant enrollment, facilitators will receive training from an MI expert to ensure competency [57, 58].

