### Procedure

Eligible individuals enrolled in the study will be randomized, using a computer-generated random number sequence, to receive MIGT along with either oxytocin or placebo administration prior to each session. Each member of a specific MIGT cohort will receive the same study drug as the other members of that cohort, and members of each MIGT cohort will receive the same study drug for all six sessions. Blinding procedures will be controlled by Wellspring Compounding Pharmacy (Berkeley, CA, USA).

Previous work has shown that intranasal oxytocin administration begins to have physiological effects within 30 min and lasts for at least 90 min [35]. Thirty minutes prior to beginning each MIGT session, the study physician will administer the study drug (Wellspring Compounding Pharmacy, Berkeley, CA, USA) intranasally using a mucosal atomization device (MAD300; Teleflex technologies, Mooresville, NC, USA) attached to a 1-mL Luer-lock syringe. The oxytocin will be prepared as 40 International Units (IU) of oxytocin per 1 mL. Participants will receive 1 mL total, with 0.5 mL administered in each nostril using two separate syringes (with 0.06 mL additional drug in the first syringe to account for the MAD300 dead space). The administration procedures are consistent with recommendations for standardized intranasal drug administration [64]. Study drug administration will occur with all members present in the group therapy space, and the order of administration to individuals within a cohort will be randomized at each session.

To test tolerability to the study drug, participants will complete an Oxytocin Side Effect Checklist (OTSE), a list of 21 possible side effects [37] and the opportunity to report any other adverse effects, after each MIGT session. In addition, participants will be asked after each session to guess whether they have received oxytocin or placebo.

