### Limitations and future directions

The current study will only include men who identify as having sex with men; therefore, results may not generalize to other genders and sexual orientations. There may be further selection bias regarding the motivation and engagement of participants who choose to take part in our study protocol. Furthermore, studies with substance use disorder populations often must deal with missing data from attrition. Our self-report measures increase the risk of reporting bias, although objective measures of psychophysiology will also be examined. Lastly, group therapy studies present inherent complications regarding statistical analyses. We will take these factors into account, although likely at the expense of statistical power. Despite these limitations, this study has many novel features and effect sizes will contribute to ongoing research. Future goals involve the further development of oxytocin-enhanced psychotherapy and expanding this treatment modality to other patient populations.

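### The stated 80% power at d = 0.81 assumes 50 independent men, but the drug is fixed by therapy cohort, so the design does not deliver it; the figure for d = 1.44 is only mildly optimistic

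*Protocol article*

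**What the plan says.** All references are to the protocol article.

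- **Power analysis.** "A sample size of 25 per treatment condition will provide us with > 99% power" for "the large between-condition effect size (*d* = 1.44) observed for attendance from our preliminary 3-week trial in cocaine users", "with a two-tailed alpha = 0.05". It adds that "this sample size will provide 80% power to detect an effect size of 0.81 or greater". Cohort size, number of cohorts, ICC and design effect do not enter the statement.
- **Abstract, Methods/design.** "Individuals will be randomized (1:1) to receive six, weekly sessions of MIGT with or without oxytocin".
- **Procedure.** "Each member of a specific MIGT cohort will receive the same study drug as the other members of that cohort", and this holds for all six sessions.
- **Motivational interviewing group therapy (MIGT).** Groups are closed to new members and consist of two co-facilitators "along with four to six group members".
- **Data Analysis Plan.** The primary outcome, present or absent at each session, is compared by generalized estimating equations that allow for repeated observations on a man and for cohort membership.
- **Limitations and future directions.** On the statistical complications of group therapy: "We will take these factors into account, although likely at the expense of statistical power". No size is given.

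**The concern.** The power statement and the design rest on different models. The power figures treat each man as an independent unit. Under the Procedure section the drug varies only between cohorts, so any cohort-to-cohort variation in attendance enters the treatment comparison directly. This is so whether whole cohorts are randomized or men are randomized and then grouped within arm: either way cohorts are nested in drug. Measuring each man at six sessions does not average cohort variation away.

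Some within-cohort correlation is plausible on the article's own account. The outcome is attendance at a shared group, the therapy works through interaction among members, and the Setting and study population section accepts that participants may already know each other.

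Attendance is the one outcome with a directional hypothesis; the secondary outcomes are declared exploratory. The sensitivity that the article claims for this comparison is therefore the figure that readers, and planners of later trials, would take from it.

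**Working it through.** **Inputs from the article.** 25 men per arm; two-sided alpha 0.05; d = 0.81 (stated power 80%) and d = 1.44 (stated power >99%); cohorts of 4 to 6. Fifty men make 50/6 = 8.3 to 50/4 = 12.5 cohorts, so about 8 to 12, or 10 at five men each.

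**Assumption.** The ICC is not given. The range 0.05 to 0.20 is assumed, with 0 and 0.01 shown for reference.

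**Step 1: reproduce the stated figures.** Independent two-sample t-test, noncentrality = d × √(n/2), df = 2 × 25 − 2 = 48.

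- d = 0.81: 0.81 × √12.5 = 2.864, power 80.1%.
- d = 1.44: 1.44 × √12.5 = 5.091, power 99.9%.
- Effect detectable with 80% power: 0.809, which rounds to the stated 0.81.

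The figures reproduce without any cohort term.

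**Step 2: put the cohorts in.** Design effect DE = 1 + (m − 1) × ICC; effective n per arm = 25/DE; noncentrality = d × √((25/DE)/2). Two choices of degrees of freedom bracket the answer:

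- (a) keep 48 df, so that only the design effect acts;
- (b) use cohort-level df, number of cohorts − 2 = 10 − 2 = 8.

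Example, m = 5, ICC 0.10: DE = 1.40; 25/1.40 = 17.9; noncentrality at d = 0.81 is 0.81 × √8.93 = 2.420; power 66% on 48 df and 57% on 8 df.

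Cohorts of five (each cell: 48 df / 8 df):

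| ICC | DE | Effective n per arm | Power, d = 0.81 | d detectable at 80% | Power, d = 1.44 |
|---|---|---|---|---|---|
| 0 | 1.00 | 25.0 | 80% / 71% | 0.81 / 0.91 | 99.9% / 99.3% |
| 0.01 | 1.04 | 24.0 | 79% / 69% | 0.82 / 0.92 | 99.8% / 99.1% |
| 0.05 | 1.20 | 20.8 | 73% / 63% | 0.89 / 0.99 | 99.5% / 98.1% |
| 0.10 | 1.40 | 17.9 | 66% / 57% | 0.96 / 1.07 | 98.8% / 96.3% |
| 0.20 | 1.80 | 13.9 | 55% / 47% | 1.09 / 1.21 | 96.1% / 91.2% |

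**Step 3: vary the cohort size**, 25 men per arm, ICC 0.05 to 0.20, d = 0.81. With cohorts of four, power is 74% to 60% (48 df) or 68% to 54% (cohort-level df, 10.5). With cohorts of six, it is 71% to 51% or 58% to 41% (cohort-level df, 6.3).

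**Step 4: check basis (b) by simulation.** 40,000 runs, five cohorts of five per arm, t-test on cohort means, d = 0.81: power 70.8%, 63.2%, 56.5% and 46.7% at ICC 0, 0.05, 0.10 and 0.20, in agreement with the 8-df column.

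**Limit of the check.** Like the article's own calculation, it uses Cohen's d for a continuous summary of attendance. The planned model is for repeated yes/no attendance, so the results approximate its power.

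**The case against.** **The article already admits the loss.** It does: the Limitations section warns of lower power and the Data Analysis Plan corrects for cohort. So the analysis is not at fault, and a reader who inferred that the trial ignores clustering, with an inflated type I error, would be wrong. But the warning carries no number and leaves the Power analysis figures standing.

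**The lead claim concerns d = 1.44, and it nearly survives.** This stands. With cohorts of five and the design effect alone, power stays above 99% up to an ICC a little below 0.10; with 8 df it falls below 99% between ICC 0.01 and 0.02 but is still 91% at 0.20. A reader might infer that the trial is underpowered for its own planning effect, or that the >99% claim must be struck out. These figures do not support that.

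**The larger losses come from a test that the article does not plan.** Also fair. The Data Analysis Plan names no cohort-level test or degrees of freedom, and at ICC 0 the fall from 80% to 71% is due to the choice of df alone. With about ten clusters a small-sample correction is sound practice, so the 8-df figures are a reasonable pessimistic bound, but not the only answer.

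**The ICC is unknown.** True, and at ICC 0.01 on 48 df the power is 79%, close to the claim. This leaves the size of the shortfall open, but not its direction.

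**A null result would not be misread.** A reader might infer that a null result will be taken to exclude d of 0.81 or more. The article says nothing of the kind, and a cohort-adjusted confidence interval would show what is excluded. The point rests on the prospective claim alone.

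**Conclusion.** The 80% power at d = 0.81 is wrong as written for this design. The arithmetic is correct, but for independent men, and neither the allocation of drug by cohort nor the cohort-corrected analysis matches that model. On the t-test basis that reproduces the claim, power is below 80% at any positive ICC.

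With about 10 cohorts of five and an assumed ICC of 0.05 to 0.20, power at d = 0.81 is about 73% to 55% by design effect alone and 63% to 47% with cohort-level df. The effect detectable with 80% power rises from 0.81 to about 0.89 to 1.09, or 0.99 to 1.21. The >99% figure at d = 1.44 is only mildly optimistic: about 99.5% to 96%, or 98% to 91%.

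The direction follows from the article alone. The size rests on the assumed ICC, the df basis, and the approximation of attendance by a continuous summary.

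**What to change.** Keep 50 men and rewrite the Power analysis paragraph so that it states the cohort size, the number of cohorts, the assumed ICC range and the df basis. For example:

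*With 25 men per arm in about 10 cohorts of five and an assumed cohort ICC of 0.05 to 0.20, approximate power for d = 0.81 is 55% to 73% allowing for the design effect only (48 df), or 47% to 63% with cohort-level degrees of freedom (about 8). The effect detectable with 80% power is about 0.89 to 1.09, or 0.99 to 1.21, respectively. Power for d = 1.44 is about 96% to 99.5%, or 91% to 98%. These are approximations for a continuous summary of attendance.*

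The minimum alternative is to keep both existing figures and label them as assuming independent men, with a pointer to the Limitations section.

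The cost is one paragraph and a less favourable power statement. The sample size, the conduct of the trial and the planned analysis do not change. The cohort correction should stay: in the same simulation, a t-test that ignored cohorts had a type I error of about 7%, 10% and 15% at ICC 0.05, 0.10 and 0.20.

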### Setting and study population

Previous evidence suggests that oxytocin administration may lead to different outcomes based on the gender [59] and sexual orientation [60] of recipients. To control for this, we limited study participation to men who have sex with men (MSM). Fifty MSM who meet the criteria for MUD will be enrolled in the current study. Participants will be recruited from community mental health programs specializing in this clinical population in San Francisco, CA, USA, including the San Francisco AIDS Foundation, the Alliance Health Project, the Positive Health Program HIV/AIDS Clinic, as well as from study flyers posted in the community. Due to the specificity of our patient population, we acknowledge that participants may recognize each other or even belong to the same social circles. While we do not formally measure pre-existing relationships among those assigned to the same therapy cohort, we do take steps to ensure that intimate partners are not assigned to the same therapy cohort by collecting names of intimate partners as well as any community member that each potential participant would *not* want to be enrolled with in group therapy.

### Inclusion and exclusion criteria

The inclusion criteria are: (1) 18 to 65 years old, (2) male-identified, (3) history of sexual contact with men, (4) meet *Diagnostic and Statistical Manual of Mental Disorders, fifth edition* (DSM-5) criteria for severe MUD, and (6) considering initiating treatment for MUD or initiated treatment within the past month. Excluded from this study are individuals with: (1) a diagnosis of bipolar I disorder, (2) evidence of opioid use within the past month, (3) severe alcohol use disorder with withdrawal symptoms, (4) suicidal ideation with intent or plan or homicidal ideation within the past 90 days, (5) suicide attempt in the past 6 months, (6) cognitive impairment or behavioral issues precluding participation in group therapy, (7) diseases likely to influence hormonal or neuroendocrine status or taking hormone supplements, (8) conditions preventing nasal spray administration (e.g., nasal obstruction or frequent nose bleeds), and (7) allergies to E216, E218, or chlorobutanol hemihydrate (preservatives in nasal spray).

### Identification of target sample (eligibility screen)

Interested individuals will undergo initial screening for eligibility using a brief, structured telephone interview. To determine full eligibility, participants will attend an initial in-person assessment where informed written consent will be obtained by study staff prior to any study procedures. See Fig. 1 for study flow diagram. Sociodemographic variables will be collected by a clinical assessor, including: age, gender identification, sexual orientation using the Kinsey Scale [61], race, education, employment status, annual income, living situation, relationship status, HIV status, medical history, and medications. The subsections of Major Depressive Disorder, Manic Episodes, Alcohol Use Disorder, Substance Use Disorders, and Psychotic Disorders of The Mini International Neuropsychiatric Interview (MINI) 7.0.0 [62] and the Suicide subsection from the Structured Clinical Interview for DSM-5 (SCID-5) [63] will be administered. Participants will provide a urine sample and undergo additional clinical interviews and self-assessment questionnaires at this initial visit. A study clinician will perform a brief medical examination, including examination of the nasal mucosa.

**Fig. 1 Fig1:**
[figure not shown]
Study flow diagram

### Procedure

Eligible individuals enrolled in the study will be randomized, using a computer-generated random number sequence, to receive MIGT along with either oxytocin or placebo administration prior to each session. Each member of a specific MIGT cohort will receive the same study drug as the other members of that cohort, and members of each MIGT cohort will receive the same study drug for all six sessions. Blinding procedures will be controlled by Wellspring Compounding Pharmacy (Berkeley, CA, USA).

Previous work has shown that intranasal oxytocin administration begins to have physiological effects within 30 min and lasts for at least 90 min [35]. Thirty minutes prior to beginning each MIGT session, the study physician will administer the study drug (Wellspring Compounding Pharmacy, Berkeley, CA, USA) intranasally using a mucosal atomization device (MAD300; Teleflex technologies, Mooresville, NC, USA) attached to a 1-mL Luer-lock syringe. The oxytocin will be prepared as 40 International Units (IU) of oxytocin per 1 mL. Participants will receive 1 mL total, with 0.5 mL administered in each nostril using two separate syringes (with 0.06 mL additional drug in the first syringe to account for the MAD300 dead space). The administration procedures are consistent with recommendations for standardized intranasal drug administration [64]. Study drug administration will occur with all members present in the group therapy space, and the order of administration to individuals within a cohort will be randomized at each session.

To test tolerability to the study drug, participants will complete an Oxytocin Side Effect Checklist (OTSE), a list of 21 possible side effects [37] and the opportunity to report any other adverse effects, after each MIGT session. In addition, participants will be asked after each session to guess whether they have received oxytocin or placebo.

#### Substance use data collection

A urine sample will be collected at each study visit. A point-of-care, Clinical Laboratory Improvement Amendments (CLIA)-waived, 10-panel, Toxicology iCup Dx drug screen (Alere Inc., Waltham, MA, USA) will be used to screen samples for methamphetamine and other common substances of abuse.

#### Audiovisual data collection

Audio and video of each 90-min MIGT session will be recorded. The audio recording will be captured using the Blue Yeti USB omnidirectional microphone (Bluemic, Westlake Village, CA, USA) and recorded using Audacity audio software (Version 2.1.3, 2017) at a sample rate of 48,000 Hz. Each co-facilitator and group member will be video recorded individually using a Google Nexus 7 Tablet (Google, Menlo Park, CA, USA) equipped with a 5.0-MP camera and recorded at a 1280 × 720 resolution and 30 frames per second.

#### Psychophysiology data collection

Participants and co-facilitators will each be equipped with a Zephyr™ BioHarness v3.0 (Zephyr Technology, Auckland, New Zealand), wearable, wireless, psychophysiology data collection equipment. Once a clear signal is established, participants will be comfortable seated for a silent, 5-min baseline physiology recording. The Zephyr™ TEAM System using OmniSense Software (Version 4.2.4) will record a continuous electrocardiogram (sampled at 250 Hz), respiratory rate, temperature, and three-axis accelerometry to measure posture and activity level throughout each 90-min MIGT session.

Psychophysiology data will be pre-processed using MindWare HRV software (v3.1.2, MindWare Technologies, Ltd., Gahanna, OH, USA). Artifacts will be identified via MindWare’s dual MAD/MED and IBI Min/Max artifact detection algorithms derived from established strategy [65] and then processed manually. High-frequency heart rate variability (HF-HRV) is used as an indicator of parasympathetic nervous system activity and a primary psychophysiological variable of interest with regard to human social behavior. HRV is reduced in methamphetamine users when compared to matched healthy controls [66], and oxytocin has been previously shown to increase HRV via variable changes of increased HF-HRV and decreased Detrended Fluctuation Analysis (DFA-1), which measures how “self-similar” the data are [67]. Evidence suggests that autonomic cardiac control may moderate the relationship between oxytocin and social behavior, and HRV may play a key role in psychiatric patient response in treatment trials of oxytocin [68].

#### Self-assessment measures

Participants will complete self-assessment measures on Google Nexus 7 Tablets via Research Electronic Data Capture (REDCap), an online data capture tool, hosted by the University of California, San Francisco. At the initial visit, participants will be asked their preferred term for methamphetamine, and all future references to the drug in self-assessment questionnaires will use the individual respondent’s preferred term. The timing of administration of self-assessment measures is shown in Fig. 2.
*Social and group cohesion measures*
1.1The Group Questionnaire (GQ) [69], a 30-item measure of the quality of the therapeutic relationships in a group setting1.2The Social Provisions Scale (SPS) [70], a 24-item measure of the degree to which respondents’ social relationships provide various dimensions of support1.3The Inclusion of Others in the Self (IOS) [71], a measure assessing perceived interpersonal connectedness to various “others” for which respondents choose one in a series of images of increasingly overlapping circles. The current study measures participants’ relationships with: methamphetamine, methamphetamine-using communities, the LBGTQ community, their most intimate relationship, and their family of origin. The final administration of this questionnaire also asks about their relationship with their MIGT cohort for the study1.4The Sexual Risk-Taking Behavior (SRTB) questionnaire [9, 72] will be used to conduct a structured interview to assess risky sexual behaviors over the past 6 weeks. This measure asks the same questions regarding sex while sober and sex while under the influence of methamphetamine

*Stress reactivity measures*
2.1The Six-Item State-Trait Anxiety Inventory Short Form (STAI-6) [73], a validated measure of the three highest anxiety-present and three highest anxiety-absent items from the state portion of the full State-Trait Anxiety Inventory [74]

*Substance use measures*
3.1The Methamphetamine Craving Questionnaire-Brief (MCQ-Br), adapted from the Stimulant Craving Questionnaire-Brief [75], a 10-item measure of methamphetamine craving using a 7-point Likert scale3.2Self-reported methamphetamine use as measured by a Timeline Follow Back (TLFB), self-administered in our protocol [76], an assessment of daily use estimates for alcohol and other substances over the past 7 days [77]3.3The Readiness to Change Questionnaire (RTCQ) [78], adapted for methamphetamine users, is a 12-item measure based on the stages-of-change model [79]

